#### Full Analysis Set

All enrolled subjects, that is the ITT population plus subjects whose study intervention has never started (group A) or who don't have reached a time when the study intervention could have started (group B). All variables of all subjects not belonging to the ITT population are analyzed by descriptive statistics, provided that the number of the corresponding subjects is higher than 5, otherwise a narrative presentation of these cases takes place.

#### Handling of Implausible Values and of Missing Values

Implausible values have to be identified during the data management process in agreement with the clinical investigator. They will be converted into missing values.

Missing values will be replaced only in the ITT population and only for the three primary endpoints. The replacements will be made according to the worst-case principle (use of the worst assessed value in the study).

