• Signed informed consent prior to randomization	• Left bundle branch block
• Fluid in German	• Chemotherapy or radiation with other indications than breast cancer diagnosis
	• Current pregnancy or plans to become pregnant within the next 3 years
	• Neurodegenerative disease

All assessments are conducted at three main time points (t_0_, t_1_, t_2_) in both groups.

t_0_ (Pre): Before first chemotherapy within ± 14 days.t_1_ (interim): After 6 months ± 14 days.t_2_ (post): After 12 months ± 14 days (end of intervention).

For participants in all groups, clinical assessments during the intervention period are additionally performed at least every second month and at each clinical visit (usual care).

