### Data Collection and Timeline/Testing Procedure

Data are collected at baseline (t_0_), after 6 months of intervention (t_1_) and after 12 months of intervention (t_2_). The patient's medical record and intended therapy, demographic (age, sex) and anthropometric data (weight, height, BMI), past medical history and current medication are collected at the start. Furthermore, the primary outcome and all secondary outcome measurements of the study are captured before the first therapy session. After 6 months of intervention (t_1_), an interim exercise test is conducted to adapt the exercise workload in Arm A and in Arm B for equality. At (t_2_) the primary outcome measures and all secondary outcome measures are re-assessed. A follow-up period of 12 and 24 months is provided after the end of the intervention. The follow-up assessments therefore are parameters assessed within the clinical routine amended by the questionnaires used to assess quality of life and activity level.

A detailed study schedule is presented in Supplementary Appendix 1.

All assessments except exercise testing are performed at the Kepler University Hospital, Linz (AUT). At (t_0_), (t_1_), and (t_2_). All blood samples are drawn and stored at minus 85°C at the Kepler University Hospital Linz. Analyses of cancer-related pro- and anti-inflammatory biomarker samples are performed at the Sports University of Cologne.

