### Analysis Populations

#### Intent-To-Treat (ITT) Population

All subjects whose study intervention has actually started (group A) or who have reached a time when the study intervention could have started (group B) will be included in the ITT population. All variables will be analyzed.

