#### Per-Protocol (PP) Population

All subjects without occurrence of any drop-out situation (all valid cases) will be included in the PP population. All variables will be analyzed. The PP analysis is paramount.

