#### Group Comparisons of Further Variables

All other variables will be analyzed by usual parametric and non-parametric tests for univariate comparisons of independent samples.

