#### Regression Analyses

The influence of exercise and exercise test results on overall survival and disease-free survival will be investigated by cox regression analyses. Multiple regression analyses will be used to investigate the influence of baseline characteristics and any specific findings during the intervention phase on the primary endpoints in group A.

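### For continuous secondary endpoints the 12-month ITT comparison is an unadjusted observed-case test close to per-protocol, with no stated role for exit measurements or joint use of 6-month values

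*Protocol article*

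**What the plan says.** All places are in the protocol article.

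- **Missing values** (Handling of Implausible Values and of Missing Values): "Missing values will be replaced only in the ITT population and only for the three primary endpoints". The method for those three endpoints is worst-case substitution.
- **Tests** (Group Comparisons of Further Variables): "All other variables will be analyzed by usual parametric and non-parametric tests for univariate comparisons of independent samples". The exception is survival (Regression Analyses): "The influence of exercise and exercise test results on overall survival and disease-free survival will be investigated by cox regression analyses".
- **Populations.** ITT is "All subjects whose study intervention has actually started (group A) or who have reached a time when the study intervention could have started (group B"). For PP: "All subjects without occurrence of any drop-out situation (all valid cases) will be included in the PP population". Both sections say that all variables are analysed, and PP is given priority.
- **Leaving the study** (Drop-Out Procedure): participation ends after more than five consecutive weeks of missed HIIT. Patients who drop out are asked for all endpoint measurements when they leave.
- **6-month data.** Study Population and Recruitment says: "All assessments are conducted at three main time points (t_0_, t_1_, t_2_) in both groups". Data Collection and Timeline/Testing Procedure describes for t1 only that "an interim exercise test is conducted to adapt the exercise workload". It also has a fragment naming all three visits next to the sentence on blood samples, and it places re-assessment of the primary and all secondary measures at t2.
- **Status** (Type I Error Adjustment): everything outside the three primary hypotheses is descriptive.

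**The concern.** A two-sample test at 12 months can use only patients who have a 12-month value. With replacement ruled out, a patient who leaves after the 6-month visit adds nothing to the 12-month ITT comparison of fitness, fatigue, quality of life, biomarkers or imaging, unless her exit measurement is counted as a 12-month value. The article does not say whether it is. If it is not, ITT and PP rest on nearly the same patients, and agreement between them says little about robustness. If it is, values from arbitrary months, possibly during chemotherapy, are read as 12-month values.

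The termination rule makes this more than a formality. Only arm A has HIIT sessions to miss, so the rule can remove only arm A patients. Missing sessions is plausibly linked to poor fitness and fatigue, which are themselves secondary outcomes. An apparent benefit of exercise could then arise partly because the less fit or more fatigued arm A patients have left.

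This is a rule the article fixes, not a detail left to an analysis plan. The authors do plan a baseline-adjusted ANCOVA for the CVLT scores but do not extend it to the other outcomes.

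**Working it through.** **1. Who is in the 12-month comparison of a continuous secondary endpoint?**

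| Patient | PP | ITT as written |
|---|---|---|
| Completes t2 | yes | yes |
| Leaves, no exit measurement | no | in the population, but no value to analyse |
| Leaves, exit measurement taken | no | only if the exit value counts as t2 (unstated) |

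The two analyses can differ only in the last row.

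**2. Inputs for the size.** The article gives no figure on this point. From the article: 126 patients randomised 1:1, so 63 per arm, and expected drop-out of 15% (20% for the larger total of 134). Assumed: correlation 0.5 between t0 and each later visit and 0.65 between t1 and t2; drop-out only after t1; 20–25% in arm A with odds ratio 2–3 per SD worse 6-month score; 5–10% in arm B, unrelated to the score; no true effect.

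**3. Bias by formula.** Let d be the arm difference in mean 6-month score, in SD, that selection creates among patients still observed at t2. To first order:
- raw t2 values: 0.65 × d
- change from baseline: (0.65 − 0.50) × d = 0.15 × d
- ANCOVA on baseline only: (0.65 − 0.5 × 0.5) × d = 0.40 × d
- joint model of t1 and t2 given baseline: 0, because drop-out depends only on the observed t1 value

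Simulated bias of the raw test is about 0.09 to 0.15 SD (repeat runs put the lower end at 0.08 to 0.09). So d is 0.09/0.65 = 0.14 to 0.15/0.65 = 0.23. Then change score: 0.15 × 0.14 = 0.02 to 0.15 × 0.23 = 0.035. Baseline ANCOVA: 0.40 × 0.14 = 0.056 to 0.40 × 0.23 = 0.092.

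**4. Simulation (4,000 runs per scenario, two-sided 5% test).**

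| Analysis at t2 | Bias (SD) | Rejections |
|---|---|---|
| Two-sample, raw t2 | 0.09–0.15 | 7–12% |
| Two-sample, change from baseline | about 0.03 | 4–6% |
| Complete-case ANCOVA on baseline | 0.06–0.09 | 6–9% |
| Joint model with t1 | at most 0.006 | 4.6–5.7% |

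**5. Other assumptions.**
- Same rate and same dependence in both arms: no bias.
- Same dependence, unequal rates: raw-test bias 0.04 SD (20% vs 10%, odds ratio 2) and 0.12 SD (25% vs 5%, odds ratio 3).
- All visit correlations equal at 0.5 or 0.7, drop-out dependent on t1 in arm A only: raw-test bias 0.08–0.11 SD at about 19% vs 15% drop-out and 0.12–0.17 SD at about 29% vs 5%. By the formula in step 3 the change-score bias is then zero, since the two correlations cancel.

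**6. Precision.** In step 4 the SD of the estimate falls from about 0.19 to 0.16–0.17. Baseline adjustment alone gives 0.19 × √(1 − 0.5²) = 0.165, so almost all the gain comes from baseline. What the t1 values add is protection against bias. At 15% drop-out, 63 × 0.85 is about 53.5 per arm. The effect detectable with 80% power at two-sided 5% is (1.96 + 0.84) × √(2/53.5) = 0.54 SD unadjusted. It is 0.47 SD with baseline correlation 0.5 (× √0.75) and 0.39 SD with 0.7 (× √0.51).

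**The case against.** The case against a stronger claim is good, and most of it stands.

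- **Change scores.** Secondary Endpoints defines the exercise outcomes as changes in performance, and a two-sample test of change is compatible with the plan. Under the same assumptions its bias is only about 0.03 SD. The 0.09 to 0.15 SD therefore cannot be presented as the bias of the planned test in general.
- **Descriptive status.** Rejection rates above 5% have no confirmatory consequence. This lowers the severity, but a descriptive estimate or its confidence interval is displaced just as much.
- **ITT is not simply the completers.** A reader might infer that the two sets coincide. Exit measurements can place a drop-out in ITT but not in PP, so the documents do not support that. The gap is the unstated status of those values.
- **6-month values are not shown to be discarded.** Nothing confines the two-sample tests to t2, so a separate comparison at t1 is possible. What is absent is joint modelling. Collection at t1 is clear only for exercise tests and blood samples. For fatigue, quality of life and imaging the sections conflict, and the detailed schedule is in a supplementary appendix that is not shown.
- **Survival endpoints** get Cox regression and are outside this point.
- **Favourable simulation.** All drop-out occurs after t1 and depends only on the observed t1 value. The five-week rule can also act before t1, and no use of t1 data repairs that.

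**Conclusion.** The point holds for continuous secondary endpoints only. Their 12-month ITT analysis is, by the article's own rules, an unadjusted observed-case comparison close to PP. It is separable from PP only through exit measurements whose role is unstated. It does not use baseline as a covariate or link 6-month to 12-month values.

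The size depends on assumptions the documents do not supply. With correlations of 0.5 and 0.65 and arm-unequal drop-out after t1, bias is about 0.09 to 0.15 SD for raw values, 0.06 to 0.09 SD for baseline ANCOVA and about 0.03 SD for change scores. It vanishes if drop-out is the same in both arms. It would be wrong to conclude that a biased secondary result has been demonstrated: unequal, outcome-related drop-out is plausible from the termination rule but not established. Severity is low to moderate.

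**What to change.** In the sections on missing values and on further variables:

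1. Make the ITT analysis of each continuous secondary endpoint baseline-adjusted. For outcomes measured at t1 and t2 (at least exercise-test variables and blood biomarkers), use a mixed model for repeated measures with arm, visit, arm-by-visit and baseline-by-visit terms and an unstructured covariance, and report the arm difference at t2. For outcomes measured only at t0 and t2, use ANCOVA on baseline.
2. State that exit measurements outside the t1 or t2 window (±14 days) are not entered as t2 values. List them descriptively, or use them as auxiliary data in a multiple-imputation sensitivity analysis.
3. Keep the two-sample completer comparison as a sensitivity analysis.
4. Reconcile Study Population and Recruitment with Data Collection and Timeline/Testing Procedure on which assessments take place at t1.

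The cost is wording and slightly more programming; no new data are needed. The model assumes data missing at random given the observed values, which is weaker than what the present test needs. Drop-out before t1 remains uncured, and outcomes without a t1 value gain mainly precision.

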### Study Endpoints

#### Primary Endpoint

The primary endpoint is the difference from baseline (t_0_) to completion of the exercise intervention (t_2_), in the California Verbal Learning Test (CVLT) mean scores and consists of the three (sub)scores “short-delay,” “long-delay” and “total-trials 1–5” of the CVLT. The CVLT is an instrument commonly used to evaluate the individual verbal learning and memory.

The test consists of two 16-word lists. The word list A is defined as the learning-list; word list B is used to interfere (interference-list). Word list A will be read aloud to the patient 5 times, then list B will read once. After that, the patients must recall as many words as possible from list A, afterwards the semantic recall follows. After 20 min, the patient is asked to recall again as many words as possible from list A, followed by a helping recall trail. For recalling, similar, semantic and phonematic distractions and categoric prototypes will be used. There are two normed settings available for baseline and t_2_.

The (sub)scores “total-trials 1–5” ascertains the learning curve for the first word list based on 5 rounds. The “short-delay” reports the delayed recall immediately after presentation and retrieval of the second word list (as interference) and without repeating the first list. The “long-delay” is testing the recall after ~20 min.

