### Biostatistical Planning and Analysis

#### Concept

The study is based on a superiority approach with a comparison of two kinds of treatment and with three equal-ranking primary endpoints.

Treatment arms:

Treatment arm A: Endurance exercise intervention → group ATreatment arm B: No endurance exercise intervention → group B

Primary endpoints:

(1): CVLT total trials 1-5 after 12 months [-](2): CVLT short delay after 12 months [-](3): CVLT long delay after 12 months [-]

The type I error will be adjusted according to Bonferroni.

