### Statistical Methods

#### Group Comparisons of Primary Endpoints/Hypotheses Testing

If the hypothesis of normal distribution cannot be rejected (Kolmogorov-Smirnov with Lilliefors significance correction, type I error = 10%) and if homoscedasticity exists (Levene's test; type I error = 5%) a parametric analysis of covariance (ANCOVA) will be applied (type I error = 0.833% one-sided). Otherwise, a non-parametric analysis of covariance (rank analysis of covariance according to Quade) will be used (type I error = 0.833% one-sided).

Covariates are

CVLT total trials 1–5/CVLT short delay/CVLT long delay (corresponding variable) at baseline [-]BMI at baseline [kg/m^2^]Age at baseline [years]BDI II at baseline [-]STAI at baseline [-]Fatigue at baseline [yes/no]

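### Replacement is confined to the primary endpoints, so a missing baseline covariate removes a patient from the covariate-adjusted primary comparison in both the ITT and the PP set

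*Protocol article*

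**What the plan says.** The missing-value rule reads "Missing values will be replaced only in the ITT population and only for the three primary endpoints". The method is single-value: "The replacements will be made according to the worst-case principle (use of the worst assessed value in the study". The same section adds a second source of missing data, namely values judged implausible during data management: "They will be converted into missing values". It does not limit that conversion to outcome variables.

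The Concept and Hypotheses sections define the three endpoints as 12-month scores, for example "CVLT short delay after 12 months". The Primary Endpoint section is worded differently: "The primary endpoint is the difference from baseline".

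Under Group Comparisons of Primary Endpoints/Hypotheses Testing, if the assumption tests are passed, "a parametric analysis of covariance (ANCOVA) will be applied"; otherwise Quade's rank version is used. Each model has six baseline covariates: the matching CVLT score, BMI, age, BDI-II, STAI and a binary item, "Fatigue at baseline [yes/no]".

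On the analysis sets, the Per-Protocol section says "The PP analysis is paramount". Nothing is replaced in that set.

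**The concern.** The rule and the model do not fit together. Replacement is restricted to the endpoints, while the model also needs a complete row of covariates. The restriction is stated outright, so this is not a detail left open for the analysis plan: an analysis plan that filled in a BMI or a STAI total would contradict the published rule.

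The result is lopsided. In the ITT set, a patient with no 12-month CVLT stays in with the worst value seen in the study. A patient with CVLT observed at both visits but no usable STAI total drops out. At stake are some patients in the primary test and the precision they would bring. In the PP set the same deletion comes on top of the planned drop-out.

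**Working it through.** **Step 1. Which covariates does the rule leave unfilled?** Under the endpoint definition that is tested (12-month scores), all six covariates lie outside the rule. Baseline CVLT is arguable: if the endpoint is the change from baseline, the baseline score is part of it. Age will in practice always be known. That leaves four covariates clearly exposed: BMI, BDI-II, STAI and fatigue.

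**Step 2. Does a gap remove the patient?** ANCOVA regresses the outcome on arm and covariates. Quade's method regresses outcome ranks on covariate ranks and compares the residuals. Neither gives a fitted value for a patient with an empty covariate. The article does not state deletion in words, but it follows from the rule and the method together.

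**Step 3. Reproduce the planned size.** Inputs from the sample size section and Table 3: one-sided alpha 0.833% (0.025/3), power 80%, independent-samples t-test. Solving the noncentral-t power equation for n per group gives:

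| Endpoint | Delta / SD | n per group | Stated |
|---|---|---|---|
| Total trials 1-5 | 7.28 / 7.75 | 25.2 | 25 |
| Short delay | 1.65 / 2.35 | 43.9 | 44 |
| Long delay | 1.65 / 2.47 | 48.4 | 48 |

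The stated 48 per group (96 in all) is reproduced. Power at exactly 48 for long delay is 79.6%.

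**Step 4. Patients lost.** The article gives no missing rate, so q per covariate is assumed at 1-3%. Two patterns bracket the result:
- all gaps in the same patients: loss = 126 × q
- gaps independent across the four covariates: loss = 126 × [1 − (1 − q)^4]

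| q | Same patients | Independent |
|---|---|---|
| 1% | 1.3 | 3.9%, 5.0 |
| 2% | 2.5 | 7.8%, 9.8 |
| 3% | 3.8 | 11.5%, 14.5 |

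That is about 1-4 patients in the first case and 5-14 in the second.

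**Step 5. Effect on power, long delay.** This uses the t-test of the sample size section. It ignores precision gained from the covariates and any distortion from worst-case replacement.
- ITT, 63 per group: power 90.5% without loss. At q = 1-3% it is 90.2-89.5% (same patients) or 89.2-86.2% (independent).
- PP after the expected 15% drop-out, 126 × 0.85 = 107.1, or about 53.5 per group: power 84.5% without loss. At q = 1-3% it is 84.1-83.2% (same patients) or 82.8-79.0% (independent).

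At the unfavourable end (3%, independent) the PP set holds 107.1 × 0.885 = 94.8 patients, just under the planned 96.

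**The case against.** The strongest reply is that the design largely prevents the problem. The allocation envelope is opened at the earliest after baseline evaluation is complete. Patients unwilling to complete the questionnaires are excluded. Baseline measures are taken before the first therapy session. This stands, and it is why the loss is probably small. Two routes remain: a baseline value set to missing as implausible during data management, and a questionnaire filled in at a completed visit but with too few items for a total. The second is weaker, because rules for scoring with skipped items are commonly left to the full protocol or analysis plan.

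The size rests wholly on assumed rates. Independence across measures from a single baseline assessment is also unsupported, so the same-patient figures belong beside the independent ones.

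A reader might infer that the ITT comparison is no longer by randomised group. The documents do not support that. A gap in a value measured before allocation is in general unrelated to arm, and the remaining patients are still compared as randomised. The article does not say that implausibility decisions are made blind to arm, but nothing in it points to losses that differ between arms.

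A reader might also infer that the ITT analysis falls short of its planned size. It does not in the assumed range: 126 − 14 = 112 remain, against 96 needed.

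Finally, a reader might take the rule to bar filling every covariate. For baseline CVLT that is not settled, given the two wordings of the endpoint.

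**Conclusion.** The point holds in limited form. The replacement rule and the six-covariate model together drop patients who lack baseline BMI, BDI-II, STAI or fatigue, in the ITT set and in the PP set alike, and no other section of the article repairs this. At an assumed 1-3% missing per covariate the loss is about 1-4 of 126 if gaps coincide and 5-14 if they are independent. Given the baseline safeguards, the lower end is more likely. The cost is mainly precision: in the ITT set power stays above 80% throughout this range, and in the PP set it reaches 79.0% only in the least favourable case. Bias is not shown. The case for changing the text is that the defect is written into the rule and the repair is free.

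**What to change.** Add to Handling of Implausible Values and of Missing Values: in the primary-endpoint models for both the ITT and the PP set, a missing baseline covariate, including one set to missing as implausible, is replaced by a value derived from baseline data pooled over both arms, blind to arm and outcome. Name one method in advance: the pooled mean with the more frequent category for fatigue, or a prediction from a regression on baseline variables only. State in the same sentence that baseline CVLT is covered, which removes the ambiguity noted above.

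Baseline covariates are independent of allocation by design, so filling them this way does not bias the randomised comparison. No patient in the analysis set with a 12-month CVLT value would then be dropped for a missing covariate. The change does not bring back patients whom the ITT definition itself leaves out, that is, those who never reached the start of intervention. It costs one sentence and no data, and should be fixed before the arms are compared.

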### Drop-Out Procedure

Patients can quit study participation at any time and for any reason. Except for personal reasons, participation is terminated if participants miss HIIT sessions for more than five weeks in a row. In order to collect sufficient data for statistical analysis, participants are asked to undergo all endpoint measurements at the time of study drop-out.

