### Sample Size Estimations and Determination of Sample Size

The following information and assumptions are used for sample size estimations:

Use of data from the study of Andreotti et al. (72) (baseline assessments in healthy women) for group A.Postulation of a 15% change of the mean scores in group A over group B for all 3 primary endpoints (Xgroup A = 1.15 ^*^ Xgroup B).Postulation of a 7.5% change of the standard deviations in group A over group B for all 3 primary endpoints (SDgroup A = 1.075 ^*^ SDgroup B).Type I error (Bonferroni-adjusted) = 0.833% one-sided.Type II error = 20%.Independent samples *t*-test.

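### Giving every missing ITT score the single worst value in the study makes the ITT result follow drop-out imbalance, so it cannot reliably support or challenge the per-protocol result

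*Protocol article*

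**What the plan says.** The section on implausible and missing values limits replacement in scope: "Missing values will be replaced only in the ITT population and only for the three primary endpoints". It then fixes the value: "The replacements will be made according to the worst-case principle (use of the worst assessed value in the study"). The same section says of implausible values: "They will be converted into missing values". An implausible 12-month primary score therefore also receives the worst value.

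Two statements under Drop-Out Procedure bear on how much will be missing, and in which arm. One ends participation by a rule tied to the supervised sessions: "participation is terminated if participants miss HIIT sessions for more than five weeks in a row". Only arm A has such sessions. The other asks for data on leaving: "participants are asked to undergo all endpoint measurements at the time of study drop-out". The stated purpose is to have enough data for the statistical analysis.

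The per-protocol (PP) population excludes anyone with a drop-out, and the article says: "The PP analysis is paramount". The test under Statistical Methods is ANCOVA, or Quade's rank ANCOVA if normality or equal variances are rejected, at 0.833% one-sided for each of three CVLT scores.

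**The concern.** A worst-case rule sounds cautious. It would penalise the new treatment if only missing exercise-arm scores were set to the floor. Here the same floor value goes to both arms, so the penalty falls on the arm with more missing scores. If arm A loses more, a real benefit is diluted or removed. If arm B loses more, a benefit can be manufactured. Even with equal loss, a block of identical extreme values shrinks the difference and inflates the spread.

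The ITT is the only inferential analysis that retains drop-outs, so it is the check on the lead PP result. Under this rule, a null ITT could come from the floor value and a positive one from control-arm attrition. The article describes no other missing-data analysis.

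**Working it through.** **Inputs from the article.** Table 3, long delay: 10.97 ± 2.38 in B and 12.62 ± 2.56 in A, delta 1.65, pooled SD 2.47. N = 126 allocated 1:1, so 63 per arm. Expected drop-out is 15%, with 20% as the alternative, and no split by arm. "Type I error (Bonferroni-adjusted) = 0.833% one-sided"; power is 80%. Long delay is scored 0 to 16 (16-word list) and total trials 0 to 80 (5 × 16).

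**The plan's own figure.** Long delay sets the sample size. d = 1.65 / 2.47 = 0.668. n per group = 2(z₀.₉₉₁₆₇ + z₀.₈₀)² / d² = 2(2.394 + 0.842)² / 0.446 ≈ 47. The exact non-central t gives 49. The stated 48 is reproduced.

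**Shift in the estimate.** With missing fractions pA and pB unrelated to outcome, and floor value m, the filled difference is

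D = (1 − pA)μA − (1 − pB)μB + (pA − pB)m.

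Capping scores at 16 brings the complete-data difference to about 1.56, so take μA = 12.53 and μB = 10.97. Assume m ≈ 5, about 2.5 SD below the B mean (10.97 − 2.5 × 2.38 = 5.02).

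- 15% in each arm: 0.85 × 1.56 = 1.33.
- 20% A, 10% B: 0.80 × 12.53 − 0.90 × 10.97 + 0.10 × 5 = 10.02 − 9.87 + 0.50 = 0.65 (0.55 to 0.75 for m from 4 to 6).
- 10% A, 20% B: 11.28 − 8.78 − 0.50 = 2.00.
- No true effect, 10% A, 20% B: 0.10 × (10.97 − 5) = 0.60, or 0.60 / 2.38 = 0.25 SD in favour of A.

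From equal loss, each 10-point gap moves the estimate by about 0.7 in either direction, over 40% of the planned 1.65. Simulated differences agree: 1.32, 0.6 to 0.7, 2.0 and about 0.63.

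**Power and error, long delay.** Simulation with 63 per arm and scores rounded and capped. Assumptions not in the article: baseline correlation 0.5, random missingness and the split by arm. Quade figures are used because the spike of identical values triggered the plan's switch to Quade in over 99% of runs.

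| Scenario | No drop-out has a usable score | Half have one | Observed cases |
|---|---|---|---|
| Power, 15% / 15% | about 63% | about 82% | about 92% |
| Power, 20% A / 10% B | about 26% | about 64% | about 92% |
| Type I error, 10% A / 20% B | about 9% | about 3% | nominal 0.833% |

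With balanced loss, type I error stays near nominal.

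**Sensitivity to the simulation set-up.** The table lets the number missing per arm vary by chance around the stated rates. Holding it at the exact rates gives, in the column with no usable score, rank-test power of 62 to 74% at 15/15, at most 12% at 20/10, and type I error of 4 to 5% at 10/20 (baseline correlations 0 to 0.6). The direction is the same, and the error is still about five times nominal or more.

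**Total trials.** Quade power is about 91% at balanced 15% and about 60% at 20% A / 10% B, against about 99% or more on observed cases.

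**The case against.** - **The rule does not touch the lead result.** True: PP is declared paramount. The 80% power was also planned for 48 valid cases per group, which is the PP population. A reader might say the ITT loses its planned power, but no power was planned for it.
- **Drop-outs may be measured.** A reader might infer that the ITT overwrites the score taken at drop-out. The text does not say so: only missing values are replaced, and nothing says whether a drop-out score counts as the 12-month value. What stands is that this measurement has no stated role in the analysis populations, the missing-data rule or the statistical methods. If many such scores are usable, the harm shrinks, as the table shows, but does not disappear.
- **Not every endpoint suffers equally.** Total trials loses little under balanced drop-out. The damage there comes from imbalance.
- **Inflated type I error needs more loss in B.** The only arm-specific exit rule acts on A, so dilution of a real benefit is the better supported direction. Nothing in the article predicts that controls will leave more often.
- **Missing baseline covariates.** A reader might infer that women lacking a covariate fall out of the ITT ANCOVA because only primary endpoints are replaced. Envelopes are opened only after complete baseline evaluation, and patients unwilling to complete the questionnaires are excluded, so this is largely ruled out.
- **Opposite biases.** It is tempting to say that PP and ITT err in opposite directions. Since the ITT shift can go either way, this is not established.

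**Conclusion.** The concern holds for the ITT analysis of the primary endpoints. One common floor value in both arms makes the estimate depend on the difference in missingness: about 0.7 points of long delay per 10-point gap. At the protocol's own 15% overall rate, and with no usable drop-out scores, long-delay power falls from about 92% to about 63% with equal loss and to about 26% at 20% A / 10% B. Type I error rises to about 9% (4 to 5% with exact counts) at 10% A / 20% B. Half of drop-outs having usable scores reduces this to about 82%, 64% and 3%.

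These sizes rest on the assumed split, random missingness, the baseline correlation and the share of drop-outs with a usable score. The dependence on imbalance does not: it follows from the rule itself. Scoring an implausible entry as the worst performance in the study is a literal consequence of the text, though its size cannot be estimated. The PP result is unaffected, but the ITT as written cannot reliably support or challenge it.

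**What to change.** Make the ITT analysis of the three primary endpoints a missing-at-random analysis: multiple imputation by arm, or a mixed model. Use baseline CVLT, the listed ANCOVA covariates, and any interim or drop-out CVLT scores. State how the drop-out score enters, as a measurement at its own time rather than as a 12-month value. Treat implausible values as ordinary missing values in that analysis. Add a delta-adjusted (tipping-point) sensitivity analysis, and keep worst-value replacement only as an extreme sensitivity run.

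The cost is a change of wording and modest programming, with no new data. It should be settled before allocation is unblinded for analysis. The missing-at-random assumption cannot be tested, which is why the delta-adjusted analysis is needed.
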